## Abstract

**Background:**

Cold hypersensitivity in the hands and feet (CHHF) is one of the most common complaints among Asians, especially in women. Korean red ginseng (KRG), which is a steamed form of *Panax ginseng,* has vasodilating action in the peripheral vessels and increases blood flow under cold stress. However, few studies have evaluated the effect of KRG on cold hypersensitivity.

**Methods/Design:**

This trial is a randomized, double-blind, placebo-controlled trial in 80 CHHF patients. The trial will be implemented at Kyung Hee University Hospital at Gangdong in Seoul, Korea. The participants will take KRG or a placebo for eight weeks, after which they will be followed-up for four weeks. During the administration period, six capsules of 500 mg KRG or placebo will be provided twice a day. The primary outcome is change of skin temperature in the hands between baseline and after treatment. The secondary outcomes include the visual analogue scale scores of cold hypersensitivity in the hands, change of skin temperature and the VAS scores of cold hypersensitivity in the feet, the recovery rate of the skin temperature by the cold stress test of the hands, the distal-dorsal difference of the hands, power variables of heart rate variability, and the 36-item short form health survey.

**Discussion:**

This study is the first trial to evaluate the efficacy of KRG on CHHF by using infrared thermography. Our study will provide basic evidence regarding CHHF.

**Trial registration:**

CliniacalTrials.gov NCT01664156

## Background

Generally, cold hypersensitivity refers to the condition in which patients feel excessively cold at low temperatures, and cold hypersensitivity in the hands and feet (CHHF) is one of the most common complaints among Asians, especially in women. According to a previous study on the genetic etiology of CHHF, the ratio of CHHF among females to males was found to be approximately 3:2 [1]. In particular, the prevalence of CHHF in Japanese, Korean and Chinese women is 54.3%, 25% and 20%, respectively [2]. CHHF can lower the quality of life by interfering with daily activities and, according to Korean medicine, may also be related to gynecological disorders such as menstrual pain, irregular bleeding, leucorrhea and infertility [3]. The known causes of CHHF are autonomic nervous dysfunction, peripheral neuropathy, median neuritis, anemia and diabetes mellitus [4]. However, the pathophysiology of CHHF remains unknown and a uniform treatment has not been established.

The root of *Panax ginseng* C.A. Meyer has been used worldwide for thousands of years for treatment of diverse diseases including diabetes [5], postmenopausal symptoms [6] and cancers [7]. Korean red ginseng (KRG) is a steamed form of *Panax ginseng*, which suggests that chemical transformation of active physiological properties occur involving ginsenosides, polysaccharides, peptides and polyacetylenic alcohols [8]. As a consequence of these biochemical changes, KRG acquires additional physiological activities. Steaming ginseng at temperatures over 100°C, results in the production of the gisenosides Rg3 and Rg5, which are not present in raw ginseng. Moreover, steamed ginseng is more potent at inducing endothelium-dependent vasodilation and radical-scavenging [9].

Many studies have suggested that KRG benefits vascular functions. KRG and its ginsenosides had vasodilating action on peripheral vessels and increased the blood flow under cold stress in animal experiments [10]. The ginsenosides isolated from KRG have been reported to cause vasodilation in an endothelium-dependent and nitric oxide- (NO-) mediated manner in a rabbit model [11]. Especially, the ginsenoside Rg3 was proven to inhibit vascular contraction as a consequence of NO production in a rat *in vitro* and *in vivo*[12]. Besides, in humans, KRG improved the vascular endothelial dysfunction in patients with hypertension through increasing synthesis of NO [13]. In addition, according to a randomized, controlled, double-blind trial, KRG was proven to improve arterial stiffness as measured by augmentation index [14]. According to Korean medicine, KRG is considered to have a warm quality and is used as a tonic to invigorate the body and enhance the ‘*Qi*’, which subsequently improves blood flow [15].

The vasodilating action and the warm quality of KRG provide a basis for its potential efficacy on CHHF. However, only one clinical trial has evaluated the effect of KRG on CHHF [16]. In the previous trial, the participants were divided into three groups that received KRG, placebo or nifedipine (a vasodilator). The participants then submerged their hands in cold water and the time until the pain became intolerable was measured. The tolerance time to cold stress significantly increased after administration of KRG compared to the placebo and nifedipine. However, the measurement of the tolerance time to cold stress used in the previous study is a subjective assessment tool.

The aim of the current study is to evaluate the efficacy of KRG on CHHF by using an objective assessment tool, infrared thermography. The hypothesis is that KRG will reduce CHHF more effectively than placebo after eight weeks of administering either KRG or placebo. The outcome measures include changes of skin temperature and the visual analogue scale (VAS) scores of CHHF, the recovery rate (RR) of skin temperature by the cold stress test (CST) of the hands, the distal-dorsal difference (DDD) of the hands, power variables of heart rate variability (HRV), and the 36-item short form health survey (SF-36).

## Methods/Design

### Trial design

This trial is a randomized, double-blind, placebo-controlled trial in 80 CHHF patients. The trial will be implemented at Kyung Hee University Hospital at Gangdong in Seoul, Korea. The participants will take either KRG or placebo for eight weeks, after which they will be followed-up for four weeks. During the administration period, six capsules of 500 mg KRG or placebo will be provided twice a day (one hour after breakfast and dinner). A flow chart of the entire trial is shown in Figure 1.

**Figure 1 F1:**
[figure not shown]
**Study flow chart.** CHHF, cold hypersensitivity in the hands and feet; KRG, Korean red ginseng.

### Participants

#### Inclusion criteria

The patients who meet all threeof the following inclusion criteria items will be included:

(1) Females aged 16 to 60 years

(2) Females complaining of CHHF

(3) A thermal difference greater than 0.3°C between the palm and the upper arm

#### Exclusion criteria

Patients who report the following conditions will be excluded:

(1) Skin ailments, radiculopathy, thrombophlebitis and injuries affecting infrared imaging

(2) Alcohol abuse or alcoholism

(3) A history of cancer within the past five years

(4) Severe depression or mental illness

(5) Taking hypertensive or diabetic medications or thrombolytic agents

(6) Pregnant or breastfeeding

(7) Severe heart, pulmonary, hepatic and renal diseases (assessed by self-reporting and a blood test at the screening visit)

(8) Allergies to KRG or ginseng

(9) Ingestion of herbal medicine or nutritional supplements within a week before participation

(10) Participation in another clinical trial within the past three months

### Interventions

The KRG (Korean Red Ginseng powder capsule®) was manufactured by Korea Ginseng Corporation (Seoul, Korea) from the root of six-year-old *Panax ginseng* C.A. Meyer (family Araliaceae) harvested in Korea. The raw ginseng was cultivated and managed by Good Agricultural Practices established by the Rural Development Administration. The manufacture of KRG was processed according to Korean Good Manufacturing Practices and permitted and regulated by the Korean Food and Drug Administration. KRG was made by steaming fresh ginseng at 90 to 100°C for three hours, followed by drying at 50 to 80°C. KRG capsules containing KRG powder were prepared from ground red ginseng (KRG capsule, 500 mg/capsule). A total of 3 g of KRG powder contained 2 g of carbohydrates and 1 g of protein. The capsule was made of hydroxypropyl methylcellulose, pectin, purified water, sucrose fatty acid ester, glycerin, calcium gluconate and glacial acetic acid. KRG was analyzed by high-performance liquid chromatography. KRG contained the following active compounds: -Rb1, 5.61 mg/g; -Rb2, 2.03 mg/g; -Rc, 2.20 mg/g; -Rd, 0.39 mg/g; -Re, 1.88 mg/g; -Rf, 0.89 mg/g; -Rg1, 3.06 mg/g; -Rg2(s), 0.15 mg/g; -Rg3(r), 0.08 mg/g; -Rg3(s), 0.17 mg/g; -Rh1, 0.30 mg/g, and other minor ginsenosides. The standard chemical components in KRG were the total amount of Rb1 and Rg1 (6 mg/g). The examination of the remaining agricultural chemical was also conducted. The tolerance limit for pesticide residue of KRG was 0.5 mg/kg according to the regulation of Korean Food and Drug Administration. The voucher specimens were kept at the laboratory of Korea Ginseng Corporation (Seoul, Korea). The lot number of KRG that will be used in our trial is 30032005.

The participants assigned to the KRG group will be required to take six capsules of 500 mg KRG twice a day (one hour after breakfast and dinner), accounting for a total of 6 g in a day. The dosage of KRG was determined based on the total amount of Rb1 and Rg1, according to Korean Food Standards Codex. The participants assigned to the placebo group will take placebo capsules similar to the color, flavor and scent of KRG. Placebo was made of cornstarch, natural coloring (Brown CG-11771, JEY’s F.I. Inc., Sungnam Korea), brown caramel coloring (Bolak Co., Hwasong Korea) and red ginseng flavor (C80509, French Korean Aromatics Co., Yongin Korea). The lot number of placebo that will be used in our trial is 30032006. Samples of the placebo were also kept at the Korea Ginseng Corporation (Seoul, Korea). After several attempts, a placebo that could not be distinguished from the real KRG by 20 healthy persons was successfully produced. Besides, at the end of the study, all participants will be asked whether the experimental agents that they had taken were real or placebo in order to evaluate the success of blinding. In addition, the patients will be given a diary, which they will be asked to fill in twice a day, after taking KRG or placebo. The diary will be used to check their compliance to the administration. The patients’ data will be excluded from the per-protocol analysis unless their compliance rate is more than 70%.

### Objectives

The objectives of the current study are (1) to evaluate the efficacy of KRG on CHHF and (2) to establish basic evidence via the evaluation of CHHF by using objective assessment tools.

### Outcomes

#### Primary outcome

The primary outcome is a change of skin temperature in the hands between baseline (visit 2) and after treatment (visit 4). The skin temperature will be obtained by infrared thermography. For the infrared thermography examination, the patient will be asked to avoid hot showers, hot packs, smoking, exercise, acupuncture and stimulants such as caffeine for two hours before the examination. The patient will be acclimatized to room temperature (25 ± 1°C) for 15 minutes and seated comfortably on a chair without physiological or psychological stress. Subsequently, the patient will stand in an anatomical posture. Thermal images of the palm and the upper arm will be obtained to assess cold hypersensitivity in the hands. The difference between the palm and the upper arm, which is related to the severity of cold hypersensitivity in the hands, will then be calculated.

#### Secondary outcome

The secondary outcomes include the VAS scores of cold hypersensitivity in the hands, change of skin temperature and the VAS scores of cold hypersensitivity in the feet, RR of the skin temperature by the CST of the hands, the DDD of the hands, power variables of HRV, and the SF-36 between the baseline (visit 2) and after the treatment (visit 4). A 100-mm VAS measurement will be used to assess the severity of CHHF. The VAS scores will be rounded to the nearest integer in millimeters.

The CST is used to examine the function of recovery after cold stress. The patient will be seated and the baseline thermal images of the dorsum of both hands will be acquired with infrared thermography. Subsequently, both hands will be submerged up to the wrist in cold water (20°C) for a period of one minute. The hands will then be taken out of the cold water and will be carefully wiped and dried with a dry towel. Thermal images of the dorsum of both hands will be obtained immediately after immersion and six minutes later. The RR of the skin temperature at six minutes will be calculated as follows:

$$\mathrm{RR}=\left(T_{6}-T_{0}\right)/\left(T_{\mathrm{base}}-T_{0}\right)\times 100\left(\%\right)$$

T_base_: baseline skin temperature

T_0_: skin temperature immediately after cold stress

T_6_: skin temperature six minutes after cold stress

Recently, the thermographic DDD has been used as a parameter to evaluate the severity of vasoconstriction [17,18]. The DDD was calculated by subtracting the temperature of the finger from that of the dorsum [19]. Therefore, the DDD is considered positive if the finger is colder than the dorsum, and a high DDD indicates severe CHHF.

HRV is used to study the activity of the autonomic nervous system indirectly. Low-frequency (LF) power is thought to be strongly related to sympathetic nerve system activity and correlates with the regulation of blood pressure and peripheral vascular tone. High-frequency (HF) power reflects sinus arrhythmia and breathing activity and is strongly based on parasympathetic nerve system activity [20]. The ratio of LF to HF power is commonly interpreted as an indicator of the relative balance between sympathetic and parasympathetic activity, with higher ratios corresponding to higher relative sympathetic activity [21]. The total power is not a specific indicator of a particular type of autonomic nervous system expression, but is rather an indicator of the total amount of variability, which includes all of the different possible influences on heart rate variation [20].

CHHF may lower quality of life by interfering with daily life and restricting activities in the cold environment. Therefore, improving quality of life is another important goal in the treatment of CHHF. The SF-36 is a generic instrument to measure health-related quality of life and is widely used to survey physical and emotional health. The validated Korean version of SF-36 that will be used in this study was provided by the Health Assessment Laboratory (Boston, MA, USA). It consists of 36 questions grouped into eight dimensions: physical function (10 items), role limitations owing to physical health problems (4 items), bodily pain (2 items), general health perception (6 items), energy and vitality (4 items), social function (2 items), role limitations owing to emotional problems (3 items) and mental health (5 items). The number of questions for each health concept ranges from 2 to 10, and the number of response options per question is either two (yes or no) or six (none, very mild, mild, moderate, severe or very severe). Each of the dimension scores are expressed as a value between 0 and 100, with higher scores representing better health status [22].

### Safety assessment

All participants will be asked to record any adverse events in a diary during the administration and the follow-up period. All adverse events will be described in the case report form (CRF). The complete blood count (CBC), erythrocyte sedimentation rate (ESR), liver function test and renal function test will be assessed to determine the safety of the treatments at the completion of KRG or placebo administration. These analyses will be performed at an accredited laboratory. All values detected in the laboratory will be recorded by the investigator in the CRF.

### Sample size

This trial has a pilot characteristic to evaluate the efficacy of KRG on CHHF by using infrared thermography. Although there was no previous study that is the same in design, we calculated the sample size on the basis of a study that used similar variables. The previous study measured the tolerance time to cold stress to assess the efficacy of KRG on CHHF using a two-sided test, yielding a 5% significance level [16]. The formula for estimating the sample size is as follows:

$$n_{t}=n_{c}=\left\{{\left(Z_{\alpha /2}+Z_{\beta }\right)}^{2}\sigma^{2}\left(\lambda +1\right)/\lambda \right\}/{\left(\mu_{t}-\mu_{c}\right)}^{2}$$

In the previous study, the tolerance time to cold stress prolonged 0.35 minute in the KRG group compared with the control group (μ_t_-μ_c_), and a mean standard deviation (σ) was 0.84. In our study, the ratio (λ) of KRG to placebo is 1:1. With an 80% power (1-β) and a 5% significance level (α), assuming μ_t_-μ_c_ = 0.35 and σ = 0.84, a sample size of *n*_
*t*
_ *= n*_
*c*
_ = 32 patients per group is needed (*n*_
*t*
_, number of patients in KRG group; *n*_
*c*
_, number of patients in placebo group). Anticipating a drop-out rate of approximately 20%, the total sample size should be more than 80 women.

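### The 80% power claim is calculated for cold-water tolerance time, which this trial does not measure, so it is not a stated property of the primary skin-temperature test

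*Protocol article*

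**What the plan says.** The Sample size section says the trial has a pilot character and that no earlier study shared its design. It therefore works from a study whose variables it regards as similar: "The previous study measured the tolerance time to cold stress to assess the efficacy of KRG on CHHF using a two-sided test". Two inputs come from that study: "the tolerance time to cold stress prolonged 0.35 minute in the KRG group compared with the control group", "and a mean standard deviation (σ) was 0.84". The design settings are introduced by "With an 80% power (1-β) and a 5% significance level (α", with equal allocation. From these the section states that 32 women per group are needed, and then: "Anticipating a drop-out rate of approximately 20%, the total sample size should be more than 80 women".

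The Primary outcome section defines something else: "The primary outcome is a change of skin temperature in the hands between baseline (visit 2) and after treatment (visit 4"), measured by infrared thermography after the woman has acclimatised to room temperature.

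Tolerance time does not appear under Primary outcome, under Secondary outcome or among the target variables in Statistical analysis. The cold stress test used here is a one-minute immersion at 20°C followed by temperature recovery, so it does not yield a tolerance time either. The Background explains why this trial uses a different tool: "the measurement of the tolerance time to cold stress used in the previous study is a subjective assessment tool".

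**The concern.** A power statement is useful only if it refers to the comparison that decides the trial. Here the difference and SD belong to minutes until pain in cold water became intolerable, while the deciding comparison is in degrees of skin temperature. The article sets the earlier measure aside as subjective and then relies on its effect and variability for the design. It gives no target difference, SD or power in °C.

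What is at stake is how the primary result is read. The Statistical analysis section tests at P<0.05, and the Background states an efficacy hypothesis. A reader who takes the 80% at face value could treat a non-significant temperature result as coming from an adequately powered test. Nothing in the article supports that.

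**Working it through.** **Inputs from the Sample size section.** Difference 0.35 minute; SD 0.84; two-sided α = 5% (the formula uses Z for α/2); power 80%; allocation ratio λ = 1; dropout about 20%; 32 per group before dropout and 80 in total.

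**Step 1: the plan's own figure.** With λ = 1 the printed formula is n = 2(Z_α/2 + Z_β)²σ²/(μt − μc)².

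n = 2 × (1.960 + 0.842)² × 0.84² / 0.35² = 90.4, so 91 per group (about 92 with the t distribution).

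The stated 32 is not reproduced. A one-sided test gives 72. Leaving out the factor 2 gives 46 two-sided or 36 one-sided. The dropout step alone is consistent: 32/0.8 = 40 per group, 80 in total.

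**Step 2: what is being carried over.** In this formula the units cancel, and only the ratio of difference to SD matters: 0.35/0.84 = 0.42 SD. Applying the calculation to skin temperature therefore assumes that KRG shifts the temperature change by 0.42 of its own SD. The article does not state or justify that assumption.

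**Step 3: power if 0.42 SD is granted** (two-sided 5%):

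| Women per arm | Normal approximation | t distribution |
|---|---|---|
| 32 | 38% | 37% |
| 40 | 46% | 45% |

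**Step 4: what the sample delivers for any continuous outcome.** The detectable difference is the standardised difference with 80% power in a two-sided 5% two-sample t-test. The half-width of the 95% confidence interval for the difference in means is t(0.975, 2n − 2) × √(2/n), in SD units.

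- 32 per arm: detectable 0.71 SD (0.70 by normal approximation); half-width 1.999 × √(2/32) = 0.50 SD.
- 40 per arm: detectable 0.63 SD; half-width 1.991 × √(2/40) = 0.45 SD.

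The first case is the planned 20% loss. The second is an intention-to-treat analysis that includes all 80 women.

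**Step 5: in °C.** The article gives no SD for the temperature change. The SDs below are assumptions, chosen only to show the range.

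| Assumed SD (°C) | Detectable, 32 per arm | Detectable, 40 per arm | Half-width, 32 per arm | Half-width, 40 per arm |
|---|---|---|---|---|
| 0.5 | 0.36 | 0.32 | 0.25 | 0.22 |
| 1.0 | 0.71 | 0.63 | 0.50 | 0.45 |
| 2.0 | 1.42 | 1.27 | 1.00 | 0.89 |

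Across these SDs the detectable difference varies fourfold, and nothing in the article narrows it.

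**The case against.** The substitution is disclosed. The section says the trial has a pilot character, that no study of the same design existed, and that a related one was used instead. The Background identifies only one earlier clinical trial of KRG in this condition. The endpoint, difference and SD are all printed, so nothing is hidden. This part stands, and it makes the matter a weak assumption stated openly. It does not rescue the claim, because the section still says 32 per group are needed for 80% power and the analysis still tests at P<0.05.

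It can also be said that the arithmetic error is the more demonstrable fault in this section. That is fair, but it is a separate fault. Correcting 32 to 91 would still give a number tied to tolerance time.

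Three stronger readings are tempting, and the documents support none of them.

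- A reader might infer that the borrowed effect cannot apply to temperature even in SD units. The article does not show that 0.42 SD is wrong for skin temperature; it only gives no reason to think it right.
- A reader might infer that a null result would be uninterpretable. It would not be: the estimate and its confidence interval can be read whatever power was planned.
- A reader might set the 0.3°C threshold in the Inclusion criteria and Discussion beside the detectable differences and conclude that the trial is too small. That threshold is a diagnostic cut-off for a palm-to-upper-arm difference within one woman. It is neither a treatment effect nor a minimal important change.

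**Conclusion.** The point holds. The 80% power rests on an outcome that this trial does not measure, and the article gives no justification for transferring the standardised effect to the change in hand skin temperature. Power for the primary test is therefore unstated. If the transfer is accepted anyway, the claim still fails: about 37–38% power with 32 per arm and about 45% with 40, against the stated 80%.

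The power figures assume a two-sided 5% two-sample comparison and the printed inputs. The detectable differences and half-widths in SD units need no °C figure, but the °C values rest on assumed SDs. It does not follow that the trial is underpowered for skin temperature, because neither a target difference nor an SD in °C is given.

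**What to change.** Rewrite the Sample size paragraph as follows.

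- Withdraw the 80% power claim and the statement that 32 per group are needed for it. State that 80 women was set pragmatically for a pilot trial.
- Report what that size delivers for the primary outcome: detectable difference at 80% power of 0.71 SD with 32 per arm and 0.63 SD with 40, and 95% confidence interval half-width of 0.50 SD and 0.45 SD. Translate both to °C over an SD range labelled as assumed.
- State that a non-significant primary result will be read from its confidence interval and not taken as evidence of no effect.

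The cost is one reworded paragraph and a weaker claim. No patients, visits or measurements are added. The Trial status section says recruitment is ongoing, so the change can be made before results are known.

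### The printed sample size inputs give 91 patients per group, not 32; if the printed SD is right, power is about 38%, not 80%

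*Protocol article*

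**What the plan says.** The Sample size section of the protocol article sizes the trial from one earlier KRG trial, described as "using a two-sided test, yielding a 5% significance level". From that trial it takes two inputs: "the tolerance time to cold stress prolonged 0.35 minute in the KRG group compared with the control group", "and a mean standard deviation (σ) was 0.84". Both values are given again as the planning assumptions, with equal allocation, 5% significance and 80% power.

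The formula is the standard one for comparing two means, with Z for α/2. The stated result is that "32 patients per group is needed". The section ends: "Anticipating a drop-out rate of approximately 20%, the total sample size should be more than 80 women".

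**The concern.** Formula, inputs and result all stand in one paragraph, and the result does not follow from the inputs. The gap is a factor of about 2.8 (90.4 / 32), far beyond rounding.

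What is at stake is the 80% power claim. If the printed SD is correct, the trial is more likely than not to miss the very difference it was planned on. A non-significant result could then be given more weight against KRG than the design supports. The Discussion also offers this protocol as a model for later trials, so the figure may be reused.

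**Working it through.** **Inputs** (all from the Sample size section): difference 0.35 minute; σ = 0.84; λ = 1; two-sided α = 0.05, so Z = 1.960; power 0.80, so Z = 0.8416; drop-out about 20%.

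**Step 1. The printed formula with the printed inputs.**

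n per group = (Zα/2 + Zβ)² × σ² × (λ + 1)/λ / (difference)²

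= (1.960 + 0.8416)² × 0.84² × 2 / 0.35²

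= 7.849 × 0.7056 × 2 / 0.1225 = 90.4, so **91 per group**. The stated figure of 32 is not reproduced.

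**Step 2. Does another common reading give 32?**

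| Variant | n per group |
|---|---|
| One-sided 5% (or two-sided 10%), 80% power | 72 |
| 90% power, two-sided / one-sided | 122 / 99 |
| Factor 2 left out, two-sided / one-sided | 45.2 / 35.6 |
| σ²/2 in place of 2σ², two-sided / one-sided | 22.6 / 17.8 |
| 0.84 read as a variance | 108 |
| Ratio σ/difference not squared | 37.7 |

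None comes within 2 patients of 32.

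**Step 3. What would give 32?**

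- With difference 0.35, σ must be 0.35 × √(32/2) / 2.8016 = 0.4997. Going forward with σ = 0.50: 7.849 × 0.25 × 2 / 0.1225 = 32.04.
- With σ = 0.84, the difference must be 2.8016 × 0.84 / √16 = 0.588.

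The document gives neither 0.50 nor 0.59. The printed 0.84 coincides with the normal quantile for 80% power (0.8416), so Zβ may have been written in place of σ. That is a lead for the sponsor to follow and is not proven.

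**Step 4. Is the drop-out step sound?** 32 / 0.8 = 40 per group, 80 in total. This agrees with the trial size stated elsewhere in the article, so the fault lies in the 32 or in an input to it.

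**Step 5. Power under the printed inputs.**

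- 32 evaluable per group: SE = 0.84 × √(2/32) = 0.21; power = Φ(0.35/0.21 − 1.960) = Φ(−0.293) = 38.5% (37.5% by the noncentral t).
- 40 evaluable per group: SE = 0.84 × √(2/40) = 0.188; power = Φ(0.35/0.188 − 1.960) = 46.2% (45.2% by the noncentral t).
- Difference detectable with 80% power at 32 per group: 2.8016 × 0.21 = 0.59 minute, or 0.588/0.84 = 0.70 SD.
- Recruitment needed for 80% power: 91 / 0.8 = 113.75, so 114 per group and 228 in total.

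**Step 6. Power if σ is really 0.50.** At 32 per group, Φ(0.35/(0.50 × 0.25) − 1.960) = Φ(0.84), about 80%.

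**The case against.** The arithmetic is not open to dispute. The difference and the SD are each printed twice in the section, and the 32 fits the total of 80, so an error in reading the PDF is not a plausible explanation. The serious objections concern how far the conclusion reaches.

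- **The 38% is conditional.** It holds only if σ = 0.84 is the true input. If the SD was misprinted and 0.50 was meant, the power claim stands and only one figure needs correcting. Settling this needs the cited trial. This objection stands, and the conclusion is worded accordingly.
- **The 38% is the lower end.** It applies after the full 20% drop-out. An intention-to-treat analysis is also planned, and with all 40 per group analysed the power is about 46%. That stands too, but a miss rate of about 54% instead of 62% is still far from the 20% claimed.
- **The planning variable is not the primary outcome.** The inputs are minutes of cold tolerance, while the Outcomes section names change in hand skin temperature as primary. Neither 80% nor 38% is therefore the power for the primary comparison. This limits what the figures mean but does not repair the calculation.
- **The trial is described as partly a pilot.** That softens the consequence. It does not excuse the figure, because the same section claims 80% power and the article sets out a superiority hypothesis to be tested at the 5% level.

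**Conclusion.** The concern holds. The printed formula and inputs give 91 per group against the stated 32, so the SD and the sample size cannot both be right.

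If σ = 0.84 is right, power for a 0.35-minute difference is about 38% at 32 evaluable per group and about 46% at 40, against the claimed 80%. If σ was about 0.50, the sample size and power are essentially right and the printed SD is wrong. The document does not show which.

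These results assume a two-sided 5% test of two means with equal allocation, and they refer to tolerance time only. A stated power and sample size that contradict their own inputs must be corrected whichever figure proves wrong.

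**What to change.** Check the SD (and the 0.35) against the cited trial, then make one of two corrections in the Sample size section.

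- **If σ = 0.84 is confirmed:** keep 80 patients, withdraw the 80% claim, and state power of about 38% at 32 evaluable per group (46% with no drop-out). Alternatively, state the difference detectable with 80% power at 32 per group as 0.59 minute, or 0.70 SD.
- **If σ was 0.50:** correct the printed SD. Strict rounding of 32.04 gives 33 per group, but the difference from 32 is immaterial.

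In either case, say that the figures relate to tolerance time and not to the thermographic primary outcome. The cost is a correction of wording, with no need to enrol more patients. The stated power may become less favourable.
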